### Outcomes

The primary outcome will be as follows: (1) incidence of adynamic ileus (the number of patients needing postoperative nasogastric tube insertion; nausea/vomiting; or intolerance to oral feedings in the first 72 h of the surgery).

Secondary outcomes will be as follows: (1) the time to intestinal transit (time to first evacuation/flatus); (2) time to start feeding; (3) length of hospital stay; (4) grade of colitis (Harig scoring system) [25]; (5) operative complications (during hospitalization); (6) direct costs; (7) stool consistency (Bristol stool scale) [27]; (8) fecal incontinence (Wexner score) [28]; (9) abdominal cramps/pain; (10) number of evacuations per day; and (11) quality of life (SF-36) [29] and low anterior resection syndrome score (LARS) [30]. The secondary outcomes 7 to 11 will be evaluated at every clinical visit during postoperative follow-up. Patients will return after 7–14 days after surgery, followed by 1, 3 months, and 6 months. Patients will be actively investigated for secondary outcomes at each return visit. The relevant questionnaires will be applied at each follow-up visit.

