### Statistical analysis

An independent author not involved in the recruitment or data collection will perform an intention-to-treat analysis in this superiority controlled trial. Improper application of the rectal tubes will not be excluded from the analysis. The patients will be analyzed according to the group assigned in randomization, even if they drop the intervention or apply only partially (or incorrectly) the rectal stimulation solution. Qualitative variables will be described as absolute counts and percentages. Continuous variables will be described as median and interquartile range. Scores outcomes generated from questionnaires will be evaluated as discrete variables. Differences between groups will be evaluated by the Mann-Whitney test for continuous and discrete variables and Fisher’s exact test or chi-square test for categorical variables. No adjustments per baseline characteristics of the patients are intended.

The investigators will check monthly to ensure the integrity of the data quality, assessing for missing data and invalid field entries. The mean of each variable will be used to replace missing data. The Kolmogorov-Smirnov test will be used to investigate the normality distribution of the variables. For non-normal distribution, a logarithmic transformation will be performed. For sensitivity analysis, the best-worst-case scenario dataset will be generated, assuming all participants lost to follow-up in the intervention group have had a beneficial outcome and all those with missing outcomes in the control group have had a harmful outcome. Then a worst-best-case scenario dataset will be generated assuming all participants lost to follow-up in the intervention group have had a harmful outcome, and all those lost to follow-up in control have had a beneficial outcome. For continuous outcomes, a “beneficial outcome” will be the group mean plus 2 standard deviations of the group mean, and a “harmful outcome” will be the group mean minus 2.

A per-protocol analysis, in which participants who violate the protocol are excluded from the analysis, will be performed as sensitivity analysis to investigate the robustness of the results to protocol deviations.

Statistical analyzes will be performed using the Statistical Package for the Social Sciences, version 18.0 for Windows (SPSS Inc., Chicago, IL, USA).

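### The best-worst rule for continuous outcomes ignores direction, so the two missing-data scenarios are swapped for transit time, feeding time, hospital stay and costs

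*Protocol article*

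**What the plan says.** The Statistical analysis section of the protocol article replaces missing data by the mean of each variable and then plans two extreme-case datasets. The best-worst dataset is built by "assuming all participants lost to follow-up in the intervention group have had a beneficial outcome", with missing controls given a harmful one. The worst-best dataset is built by "assuming all participants lost to follow-up in the intervention group have had a harmful outcome", with missing controls given a beneficial one.

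For continuous outcomes the two terms are given numbers. A beneficial outcome "will be the group mean plus 2 standard deviations of the group mean"; a harmful outcome "will be the group mean minus 2" (standard deviations being implied). The rule has no condition on the direction of the outcome.

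The Outcomes section lists, among the secondary outcomes, "time to first evacuation/flatus); (2) time to start feeding; (3) length of hospital stay; (4) grade of colitis", followed by complications, direct costs, stool consistency, several symptom and function scores, evacuations per day and quality of life. The same Statistical analysis section says that questionnaire scores are handled as discrete variables.

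**The concern.** Adding 2 SD gives a better value only where a higher value is better. For the four outcomes that are plainly continuous, the protocol says the opposite. The Background reports shorter time to diet acceptance, shorter time to defecation and shorter hospital stay as the gains seen in earlier studies, and the Cost assessment section looks for a reduction in cost.

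Applied literally, the rule gives missing intervention patients long stays and slow transit in their supposed best case, and gives missing controls short stays and fast transit. The worst case does the reverse. A later statement that the benefit survives the worst case would then rest on the scenario most favourable to the intervention. Because the main analysis uses mean imputation, this pair is the only check on missing data that the article describes.

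**Working it through.** **Inputs from the protocol**
- Mean stay 2.5 days (stimulated) and 4.6 days (control), from the trial of 70 patients cited in the Background. Difference, control minus intervention: 2.1 days. A positive difference is a benefit.
- 52 patients per arm (Sample size). The pooled two-proportion formula for 20% against 2.8%, two-sided alpha 0.05 and power 80%, gives 53 per arm, and power at 52 is 79.7%. The stated figure is thus reproduced to within one patient. It serves here only as a denominator.

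**Assumptions, because the protocol gives no figures:** SD of 2 days in each arm and 5 of 52 missing per arm (9.6%). A range follows below.

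**General form.** Let the observed benefit be D = control mean − intervention mean, the missing share in each arm m, and the SDs s_I and s_C. Where lower is better, the rule as written gives:
- best-worst: D − 2m(s_I + s_C)
- worst-best: D + 2m(s_I + s_C)

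With the direction corrected, the two signs exchange. The reversal therefore needs only m > 0 and an SD > 0.

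**Best-worst as written**
- Missing intervention patients receive 2.5 + 2×2 = 6.5 days: (47×2.5 + 5×6.5)/52 = 2.88.
- Missing controls receive 4.6 − 2×2 = 0.6 days: (47×4.6 + 5×0.6)/52 = 4.22.
- Difference 1.33 days, which is below the observed 2.1.

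**Best-worst with the direction corrected**
- Missing intervention patients receive 2.5 − 4 = −1.5 days, which is impossible, so 0: (47×2.5 + 5×0)/52 = 2.26.
- Missing controls receive 4.6 + 4 = 8.6 days: (47×4.6 + 5×8.6)/52 = 4.98.
- Difference about 2.73 days, which is above the observed 2.1. Without truncation it would be 2.87, a figure that depends on a negative stay.

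**Range for length of stay (best-worst difference, days)**

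| SD as % of mean | Missing per arm | As written | Direction corrected |
|---|---|---|---|
| 30% | 5% | 1.89 | 2.31 |
| 50% | 10% | 1.39 | 2.81 |
| 80% | 10% | 0.96 | 3.24 |

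In the last row the imputed values include negative stays (4.6 − 2×3.68 = −2.76 and 2.5 − 2×2 = −1.5). Truncation at 0 changes that row to 4.14 subtracted from by 2.90, that is 4.14 − 2.90 = 1.24 as written, and 5.34 − 2.25 = 3.09 corrected.

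With only one patient missing per arm and an SD of 2, the figures are (235.2 − 134.0)/52 = 1.946 as written and (243.2 − 127.5)/52 = 2.225 corrected and truncated. The order is the same, but the gap is small.

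**A case where the label matters.** The Background cites time to first flatus or stool of 27.9 against 32.3 hours, a benefit of 4.40 hours. With SD 50% of the mean and 10% missing, the shift is 2×0.1×(13.95 + 16.15) = 6.02 hours. The scenario labelled best for the intervention then gives 4.40 − 6.02 = −1.62 hours, which favours control. The one labelled worst gives 10.42 hours in favour of the intervention.

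**Standard deviation or standard error.** The wording in "will be the group mean plus 2 standard deviations of the group mean" could be taken as the SD of the mean, which is smaller by a factor of √52 = 7.2.

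**The case against.** The strongest reply is that both scenarios are run. The pair covers the same two values whichever label each carries, so whether a result holds at both extremes is unaffected. That stands. The harm arises when one scenario is read by its name, which is how such results are usually reported.

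Second, a reader might infer that nearly every numeric outcome is reversed, including the colitis, incontinence, bowel-function and pain scores. The document does not support that. It handles questionnaire scores as discrete, the rule is worded for continuous outcomes, and the article gives no scoring direction for the Harig, Wexner, LARS or SF-36 scales. If the rule is meant to cover scores, any symptom score on which higher is worse is reversed as well. That part is conditional.

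Third, transit, feeding and stay are recorded during the same admission as adynamic ileus, for which the Sample size section expects no significant loss. About 10% missing is therefore pessimistic for them, and the real distortion may be small. This limits the size, not the error.

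Fourth, the planned test is Mann-Whitney with medians, so a difference in imputed means is an illustration and not the planned result. The direction carries over, because the imputed values are also ranked at the wrong end.

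Finally, the standard-error reading is a looseness of wording. The text says standard deviations, and this is not a second defect of equal weight.

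**Conclusion.** The rule is wrong as written for time to first evacuation or flatus, time to start feeding, length of stay and direct costs. For these the best-worst and worst-best labels are exchanged. On the stay example (SD 2, 5 of 52 missing per arm, both assumed) the best-worst difference is 1.33 days where the intended scenario gives about 2.73. Other assumptions change the size but never the reversal.

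A reader might go further and conclude that the main result is compromised. It is not. Adynamic ileus is binary, so beneficial and harmful need no mean or SD there. The sample size, the primary test and the main secondary analyses do not use the rule. This follows the Outcomes section, where transit time is secondary; the Abstract also names it as a primary outcome.

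Severity is moderate: a wrong rule in a sensitivity analysis of secondary outcomes.

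**What to change.** Replace the single rule by one that depends on direction:

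- Where lower is better (transit time, feeding time, stay, costs): beneficial = group mean − 2 SD, harmful = group mean + 2 SD. Where higher is better: the reverse.
- Say that the SD is that of individual observations, not of the mean.
- Bound imputed values to the attainable range: 0 for times, stay and costs, and the scale limits for scores.
- State whether the rule covers questionnaire scores. If it does, give the direction of each.
- Leave out outcomes with no single good direction (stool consistency, evacuations per day), or define benefit and harm for them separately.

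This costs a few sentences or a short table in the analysis section, settled before the data are analysed. It changes nothing in the sample size, conduct or data collection.

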### Risks and inconveniences

The additional actions performed to fulfill the protocol comprise the rectal stimulation in the interventional group, the weekly visits while administering rectal stimulation, and the rectoscopy prior to surgery. The remaining procedures and visits are performed according to the usual clinical practice. The postoperative follow-up will be the same for intervention and control groups.

No prior information suggests the risk for serious adverse events due to the trial’s intervention. The main risks associated with the procedures are colic or abdominal pain, nausea or vomiting, diarrhea, and gas. If the participant has symptoms, they will receive the corresponding medications to treat them. The research team will provide a contact for service at any time for guidance and control of symptoms related to the procedures. In the case of any serious adverse events related to the intervention, our institution and research staff will provide all the necessary care. A data safety committee will not be established for this study since this is a low-risk trial. This study will not be performed in patients with an elevated risk of death or serious adverse events. All patients will be preoperatively evaluated with standard clinical and anesthetic, and pregnant patients or patients who have any contraindication for general anesthesia or surgical intervention will be excluded (see eligibility criteria above).

Exam data are encrypted in a specific medical record system at Hospital Israelita Albert Einstein, ensuring that data confidentiality is not compromised.

### Data monitoring and management

The researchers will perform data collection. The data will be stored in a secured database using protected pathways. All data is anonymous. Only the research team will have access to the data set.

Independently on the findings of the present study, we intend to publish it in a peer-review journal. The local ethics committee does not require a data monitoring committee since only low-risk interventions will be performed. However, an audition may be performed at the discretion. No interim analyses are planned. The only stopping guideline is when the planned sample size is reached.

### Strategies to ensure data privacy

The study will follow the necessary precautions for the Brazilian General Data Protection Law (*Lei Geral de Proteção de Dados Pessoais – LGPD*; Amends Law #13,709). A data anonymization technique will be applied. The researchers will exclude information that may lead to identifying the data subject. All anonymized data will be kept under the responsibility of the coordinating researchers in an Excel file (Microsoft®) protected with a password. The researchers commit not to share the data.

### Study benefit

Suppose there is evidence of the effectiveness of probiotics and prebiotics. In that case, the patients selected for the intervention group will have received treatment to avoid postoperative symptoms, such as food intolerance.

The findings of this study may have important implications for the management of patients undergoing ileostomy reversal.

### Protocol amendments

Any amendments to the protocol will be included in the trial registry once the local ethics committee approves. The results of this trial will be published in peer-reviewed journals.

## Discussion

Adynamic ileus is a frequent postoperative complication after ileostomy reversal. Preventing this complication and improving functionality may impact the quality of life-related to bowel movements and reduce hospitalization and costs. Consequently, the findings of this randomized clinical study may have important implications for the management of patients undergoing ileostomy reversal.

Previous trials [12, 16, 31] proposed stimulus of the excluded colon via efferent ileostomy loop. This is the first controlled trial for rectal stimulus protocol with prebiotics and probiotics. The application of any intestinal stimulus by the patient demands high patient collaboration, which frequently is not easy. Patients may fail to apply the probiotics via rectal tubes properly. Thus, a per-protocol analysis would not give the most accurate depiction of the exact clinical practice applicability. The intention-to-treat analysis, as proposed for this protocol, shall provide a high level of evidence for the use of this intervention in clinical practice. The current trial may give a clear depiction of the applicability of intestinal stimulus prior to ileostomy reversal in the real world.

As a limitation, this trial will evaluate 15 days of rectal stimulation. Future studies will still be needed to determine the exact stimulation period to guarantee the rectal stimulus's highest efficacy. Other limitations include that this trial is a monocentric and unblinded study. Monocentric studies may impose some loss in external validity. However, the findings of this study may encourage the use of rectal stimulation in other institutions, and future multicentric randomized trials may contribute to the generalization of the findings of our study.

## Trial status

This is version 1 of the protocol (registration on 19 July 2022). The patient’s enrollment starts in January 2023. Considering the surgical volume in the last 3 years in our institution (25–50 ileostomy reversal procedures), we expect to finish in 2025. We intent to extend the enrolment period if necessary, until the completion of the study.

## Data Availability

No datasets were generated or analyzed during the current study. All relevant data from this study will be made available upon study completion.
